| 3                | October 8, 2019   | Protocol amended to include option to re-contact participants for up to 2 years after authorization.                                                                                                                                                                                                                                                                                                                                                                                                                                                                                                                                                                                                                                                                                                                                                                                           |
| 4                | January 24, 2020  | Added EPIC’s MyChart, emailing, and texting to recruitment methods.                                                                                                                                                                                                                                                                                                                                                                                                                                                                                                                                                                                                                                                                                                                                                                                                                            |

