| Biometrics at 3 months                                                                                                                                                                                                                                                                                                                                            | 100.0%
(22/22) | 70.8%
(17/24) | 100.0%
(45/45) | 80.0%
(44/55) | 100.0%
(42/42) | 81.4%
(48/59) |
| Dietary intake at 6 months                                                                                                                                                                                                                                                                                                                                        | 100.0%
(22/22) | 95.8%
(23/24) | 93.3%
(42/45)  | 94.5%
(52/55) | 97.6%
(41/42)  | 94.9%
(56/59) |
| Biometrics at 6 months                                                                                                                                                                                                                                                                                                                                            | 100.0%
(22/22) | 83.3%
(20/24) | 93.3%
(42/45)  | 90.9%
(50/55) | 90.5%
(38/42)  | 84.7%
(50/59) |
| Strategy 1: In-store education only. Strategy 2: In-store education plus online training and tools. % represents completion by number of subgroup participants divided by the subgroup total. Biometrics include blood pressure, weight, hip-to-waist ratio, and laboratory measurements. Overall totals for Control (N=46), Strategy 1 (N=100), and Strategy 2 (N=101). |                          |                         |                          |                         |                          |                         |

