#### **f. Statistical Analysis**

A minimum of 250 adults will be randomized into the study. Approximately 100, 100, and 50 participants will be randomized to the in-store POP education arm, the combination online/in-store POP education arm, and the control arm, respectively (see section *Data Analysis and Data Monitoring* for power calculations and testing plan).

NDSR food data will be used to calculate overall diet quality using the DASH score. The DASH score is a modification of the DASH index developed by Gunther et al. [11]. DASH score is a continuous 90-point measure with higher scores equating to higher DASH diet adherence.

Randomization will use stratification to balance important baseline covariates among study groups. These covariates will be age, sex, and household size.

Data will initially be assessed for their distribution (e.g. normality) and the level of missing values. Descriptive statistics will be calculated for each arm. The primary endpoint will be the change from baseline to Day 90 in the DASH score (as assessed by dietary intake recalls). Using hierarchical testing, up to 2 tests will be performed:

- 1) First test: Any POP education arm vs. control arm
- 2) Second test: In-store POP education arm vs. combined online/in-store POP education arm

An intention-to-treat (ITT) analysis will be used for both tests. The “last observation carried forward” approach will be used for missing data. Ascertainment of DASH score at Day 90 for each participant will require completion of at least 1 of 3 dietary intake recalls. Sensitivity analyses may be performed using a “complete case” approach or multiple imputation techniques.

The primary comparisons will use an analysis of covariance (ANCOVA) model. This multivariable model, controlling for the baseline covariates, will have DASH score as the dependent variable with treatment arm as the independent variable. As part of this process, the normality of distribution of DASH scores at both baseline and Day 90 will be assessed. If necessary, transformations (e.g. log) will be used to satisfy the assumptions of the model. The primary treatment group comparisons will be performed using appropriate contrasts of the randomization arm estimates. Statistical testing will only be performed for the second test if  $p < 0.05$  is met for the first test (i.e. hierarchical testing). This will preserve an alpha-error of 0.05.

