# COVID Impact Analyses

The effect of the COVID-19 pandemic- represented by the US national emergency declaration date of March 13, 2020- on the primary endpoint will be evaluated through these prespecified COVID-19 impact analyses with a 15% interaction significance level. The two groups are: 1) Pre-COVID (anyone with both the baseline and 3-month dietary recall timepoints occurring before 3/13/2020) and 2) During-COVID (anyone with both the baseline and 3-month dietary recall timepoints occurring after the June 2020 recruitment re-initiation).

|                             | Pre-COVID
Intervention Effect
(CI) POP1/POP2
vs. Control
(N=109) | P-value | Pre-COVID
Intervention
Effect (CI)
POP1 vs. POP2
(N=109) | P-value | During-COVID
Intervention Effect
(CI) POP1/POP2
vs. Control
(N=138) | P-value | During-COVID
Intervention
Effect (CI)
POP1 vs. POP2
(N=138) | P-value |
|-----------------------------|-----------------------------------------------------------------------------------------|----------------|---------------------------------------------------------------------------------|----------------|--------------------------------------------------------------------------------------------|----------------|------------------------------------------------------------------------------------|----------------|
| DASH Score                  |                                                                                         |                |                                                                                 |                |                                                                                            |                |                                                                                    |                |
| -Change (baseline to 3 mon) |                                                                                         |                |                                                                                 |                |                                                                                            |                |                                                                                    |                |

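### The SAP's two COVID periods do not cover every participant, yet their printed sizes account for all 247, and membership may depend on a completed 3-month recall

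*Combined protocol and SAP*

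**What the plan says.** The SAP section COVID Impact Analyses names two groups. The first is "Pre-COVID (anyone with both the baseline and 3-month dietary recall timepoints occurring before 3/13/2020" and the second is "During-COVID (anyone with both the baseline and 3-month dietary recall timepoints occurring after the June 2020 recruitment re-initiation". The table beneath is headed "vs. Control (N=109" for the first and "vs. Control (N=138" for the second. A treatment-by-period interaction is to be judged at the 15% level. The section has no third group, no rule for a participant who fits neither definition, no rule for a missing 3-month recall, and no calendar day for the June 2020 restart.

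Four other places bear on this:

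- Table S9 splits each arm into Before and During, and its footnote gives the totals: "Overall totals for Control (N=46), Strategy 1 (N=100), and Strategy 2 (N=101".
- The protocol (section 5d and Table 1) schedules the 3-month recalls on Days 85 to 99. The SAP, under Study Timepoints, accepts recalls from Day 1 up to but not including Day 166.
- Table S18 reports a Pre-COVID effect on the 3-month change in DASH score of 8.3 (95% CI 3.4 to 13.3, P = 0.001) for 22, 45 and 42 participants.
- Protocol section 5f states: "An intention-to-treat (ITT) analysis will be used for both tests".

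**The concern.** A period factor used to test whether the pandemic changed the treatment effect should be fixed by randomisation and should place everyone. The SAP's rule does neither on its face. It uses the date of a follow-up assessment, and it leaves a gap of about three months between the end of one group and the start of the other. The printed sizes nevertheless leave nobody over.

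Two things are at stake. If membership of the Pre-COVID group required a completed 3-month recall, the group was selected on an event after randomisation, and its effect describes completers. The comparison of 3-month completion in Table S9 would then be partly built into the grouping, and the interaction test would set completers against whoever remained.

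**Working it through.** **1. The printed sizes.** Inputs are the Table S9 denominators and the SAP table headings.

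| | Before | During | Sum | Arm total |
|---|---|---|---|---|
| Control | 22 | 24 | 46 | 46 |
| Strategy 1 (POP1) | 45 | 55 | 100 | 100 |
| Strategy 2 (POP2) | 42 | 59 | 101 | 101 |
| All | 109 | 138 | 247 | 247 |

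The SAP's 109 and 138 are reproduced. Nobody is unclassified, overall or in any arm.

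**2. Who the rule leaves out.** Pre-COVID needs both timepoints before 13 March 2020; During-COVID needs both after the restart. Three kinds of participant have no place:

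- baseline before 13 March 2020 and 3-month timepoint after it;
- either timepoint between 13 March 2020 and the restart;
- no 3-month recall, if a timepoint means a recall obtained.

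On the protocol schedule, Day 99 falls on 13 March 2020 for someone randomised on 5 December 2019 (13 March minus 99 days). Day 85 falls on that date for someone randomised on 19 December 2019 (minus 85 days). So a participant who kept to the schedule would straddle if randomised from some point in that fortnight up to 13 March 2020, a span of about 12 to 14 weeks (85/7 = 12.1; 99/7 = 14.1). The SAP's wider window blurs this both ways. An early recall could make a later enrollee Pre-COVID, and a Day 165 recall could make a straddler of someone randomised as early as 30 September 2019 (minus 165 days).

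**3. Who has 3-month dietary intake.** I take the Table S9 counts of dietary intake to mean that at least one recall was obtained.

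- Before: 22 + 45 + 42 = 109 of 109, so 0 missing.
- During: 20 + 47 + 49 = 116 of 138, so 22 missing (4 Control, 8 Strategy 1, 10 Strategy 2), or 22/138 = 16%.
- Most that can meet either definition if a recall must be obtained: 109 + 116 = 225 of 247.

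**4. Whether the 22 had left the trial.** At 6 months, During has 23 + 52 + 56 = 131 of 138 with dietary intake, so 7 are missing. At least 22 − 7 = 15 of the 22 therefore gave 6-month intake.

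**5. The Before group later on.** At 6 months it has 22 + 42 + 41 = 105 of 109 with dietary intake, so 4 are missing. Its 3-month record is complete, but its 6-month record is not.

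**6. A related slip in the same table.** The SAP also prints 109 and 138 above the POP1 versus POP2 columns. Those contrasts involve 45 + 42 = 87 and 55 + 59 = 114 participants; Table S18 prints 87.

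**The case against.** The strongest reply is that a timepoint can mean a scheduled timepoint. On that reading the 22 are properly in During if they were randomised after the restart, the definition selects on nothing observed later, and ordinary pandemic conditions explain the missed recalls. This stands as a possible reading. The SAP does not say that it is the intended one, and it does nothing for participants whose scheduled timepoints straddle the pause.

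Second, a reader might infer that many straddlers were put into During against the rule. The documents do not show this. They give no randomisation dates. The amendment of 24 January 2020, which added MyChart, "emailing, and texting to recruitment methods", and the February 2020 eligibility change suggest that recruitment was open, but they do not count anyone randomised. Protocol section 5d puts screening at least 30 days before randomisation, so people first reached by the new methods could not have been randomised before about 23 February. Any projected number would need an accrual start and rate that the documents do not give. Within the 247 the number could be zero.

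Third, a reader might infer that straddlers were removed and that the primary analysis is therefore not intention-to-treat. The CONSORT figure is not reproduced in the text available to me, and the minimum of 250 is a target. Whether anyone was removed before the 247 cannot be seen.

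Fourth, the 15 or more who returned at 6 months do not prove that a 3-month window was lost to the pause. The SAP's 6-month window runs to 3 September 2021, while its 3-month window closes before Day 166. The more generous window could by itself raise 6-month completion.

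Finally, the SAP's primary model does not use the COVID grouping, so the fault does not reach the primary contrast. Table S8 counts education visits, which are not part of the definition, so I make no claim that its contrast is built in.

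**Conclusion.** The COVID grouping is wrong as written, and the fault is limited to the COVID impact analysis. The definitions are not exhaustive, while the sizes printed with them are. The two agree only if a timepoint means a scheduled one and the 247 include no participant who straddled the pause or fell inside it. The SAP states neither condition.

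The size that can be established is 22 of 247 participants, all in During, who meet neither definition if a recall must be obtained. On that reading the Pre-COVID effect of 8.3 is a completers' estimate, and part of the 109 of 109 versus 116 of 138 contrast in Table S9 follows from the definition. That consequence depends on the reading; the mismatch between rule and counts in the plan's text does not. The direction and size of any bias in the 8.3 cannot be worked out from the documents.

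**What to change.** Assign every randomised participant to a period by randomisation date alone, whether or not a recall was obtained, using three strata:

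- (a) the scheduled 3-month window, to Day 99, ends before 13 March 2020 (randomised by 4 December 2019, since Day 99 is then 12 March);
- (b) randomised before the restart, with that window ending on or after 13 March 2020;
- (c) randomised on or after the restart.

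Give the restart a calendar date. Anyone randomised before it falls in (a) or (b) and everyone else in (c), so no one is left over. An early, late or missing recall does not move a participant.

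Test treatment by period on these strata in the whole-trial model. Print randomised and observed counts by arm and stratum. Correct the sizes in the SAP table, including those above the POP1 versus POP2 columns. Reconcile 247 with the number randomised. If stratum (b) is empty, that count settles the straddler question. No change to the primary model is needed.

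The cost is a revised SAP paragraph and a re-run of the COVID table and Tables S8, S9, S18 and S19, all from data already held. The Pre-COVID estimate may become less favourable, and stratum (b) may be too small to say much on its own.

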# Subgroups of Interest: Primary Endpoint at 3 Mon

| Subgroup                                           | POP1/POP2 | Control | Absolute Mean DASH Difference
(compared to Control) |
|----------------------------------------------------|-----------|---------|--------------------------------------------------------|
| Age
21-50
51-75                              |           |         |                                                        |
| Gender
Male
Female                           |           |         |                                                        |
| Race
White
Not White                         |           |         |                                                        |
| Married
Yes
No                               |           |         |                                                        |
| Education
Bachelor/Graduate
Not              |           |         |                                                        |
| Employment
Fulltime
Not Fulltime             |           |         |                                                        |
| Annual Household Income
≥\$100,000
Less      |           |         |                                                        |
| Household Size
Single Person
More            |           |         |                                                        |
| Frequency of Cooking at Home
≥5-6x/week
Less |           |         |                                                        |
| Activity level
Moderate/very
Less            |           |         |                                                        |
| Hypercholesterolemia
Yes
No                  |           |         |                                                        |
| Hypertension
Yes
No                          |           |         |                                                        |
| Obese                                              |           |         |                                                        |

|                                              |  |  |  |
|----------------------------------------------|--|--|--|
| Yes
No                                    |  |  |  |
| Baseline DASH Score
Above ≥40
Below 40 |  |  |  |

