| Obese
No
Yes                                                                                                                                                                                                                                                                                                                                                                                                                                                                                                                                                                                  | 56.7 (54.5, 59.0)
55.0 (53.0, 56.9) | 55.8 (50.4, 61.2)
50.9 (47.2, 54.6) | 0.9 (-4.9, 6.8)
4.1 (-0.4, 8.6)  | Interaction: 0.40
0.76
0.08  |
| Baseline DASH Score
< 40
≥ 40                                                                                                                                                                                                                                                                                                                                                                                                                                                                                                                                                                 | 52.4 (49.9, 55.0)
57.3 (55.6, 58.9) | 48.1 (42.7, 53.6)
53.9 (50.5, 57.4) | 4.3 (-1.8, 10.4)
3.3 (-0.6, 7.2) | Interaction: 0.78
0.17
0.10  |
| Strategy 1: In-store education only. Strategy 2: In-store education plus online training and tools. DASH score at 3 months was modeled (dependent variable) with a separate ANOVA model for each subgroup - including treatment-group (Control, Strategies 1 and 2) and subgroup x treatment-group interaction as additional terms. Imputed data was used for missing DASH scores. Data represent least-squares means (95% CI). Test for interaction effect was a two-sided F-test. Tests for differences between groups was a two-sided t-test. No adjustments for multiple comparisons were made. |                                        |                                        |                                     |                                    |

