Using 100 participants for each intervention arm (total = 200) and 50 participants for the control arm, we have 93% power to detect a 5-point difference in change from baseline in the DASH score at Day 90 between any POP education arm and the control arm. This sample size will also provide 97% power to detect a 5-point difference between the in-store and combined online/in-store POP education arms. Power estimates were done at two-sided alpha = 0.05 and assuming equal standard deviations of 9 for the primary endpoint.

All analyses will be conducted according to the statistical analysis plan (SAP). Exploratory analyses will be done for important subgroups (e.g. sex, age, race). The following table provides examples of power to detect a 5-point difference in change from baseline to Day 90 in the DASH score between the in-store and combined online/in-store POP arms for subgroups. Numerous exploratory analyses will be performed for secondary outcomes, such as dietary quality measured by the Healthy Eating Index-2015 (HEI-2015).

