|                                      | Obese (>=30 kg/m  )              |                   |                 |                 |         |
| Waist circumference (cm)             |                                              |                   |                 |                 |         |
| Hip circumference (cm)               |                                              |                   |                 |                 |         |
| Waist-to-hip ratio (WHR)             |                                              |                   |                 |                 |         |
| Total cholesterol (mg/dl)            |                                              |                   |                 |                 |         |
| HDL cholesterol (mg/dl)              |                                              |                   |                 |                 |         |
| Non-HDL cholesterol (mg/dl)          |                                              |                   |                 |                 |         |

| Variable                                                                                                                                                                                                                                                                                                                                                                                                                                                                                                                                                                                                                                                                                                                                                                                                                                                                                                                                                                                                             | Sub-Category | Control
(n=46) | POP1
(n=100) | POP2
(n=101) | P-Value |

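### The SAP examines effect modification by age, BMI and baseline DASH score only through two-level cuts; a continuous interaction term would gain about 15 to 30 points of power if the gradient is linear and the subgroups differ by 5 to 8 points

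*Combined protocol and SAP*

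**What the plan says.** The SAP table under Subgroups of Interest: Primary Endpoint at 3 Mon lists age as 21-50 and 51-75, obesity as yes and no, and starting diet quality as "Baseline DASH Score Above ≥40 Below 40". Its result columns are the combined education arms, control, and the mean DASH difference. It gives no model, no interaction term and no p-value. The only interaction test that the SAP text names is the one for COVID-19, at the 15% level.

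All three factors exist on a full scale. The SAP baseline tables list age in years and BMI in kg/m². Protocol section 5f says "DASH score is a continuous 90-point measure with higher scores equating to higher DASH diet adherence".

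The reported analysis kept the cuts. The footnote to Table S20 describes a separate ANOVA of the 3-month DASH score for each subgroup factor, "including treatment-group (Control, Strategies 1 and 2) and subgroup x treatment-group interaction as additional terms". The interaction p-values are <0.01 for age, 0.40 for obesity and 0.78 for baseline DASH.

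Protocol section 5f calls subgroup analyses exploratory. Its Table 5 gives power for comparing the two education arms inside a subgroup. No power is given for any interaction.

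**The concern.** A two-level cut treats everyone on one side of the line as alike and discards the spread within each group. If the benefit of the education rises or falls steadily with age, BMI or starting diet quality, the cut test is more likely to miss it, and a steady gradient is reported as a jump at one value.

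Control is small (46 randomised), and each cut leaves only about 13 to 15 controls on one side. What is at stake is how far the subgroup table can answer its own question of who benefits more. A non-significant interaction from such a test rules out little.

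**Working it through.** **1. The plan's own power figures.** Inputs from protocol section 5f: "Power estimates were done at two-sided alpha = 0.05 and assuming equal standard deviations of 9 for the primary endpoint"; "Using 100 participants for each intervention arm (total = 200) and 50 participants for the control arm".

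- Any education v control: SE = 9 × √(1/200 + 1/50) = 1.423; 5/1.423 = 3.514; power = Φ(3.514 − 1.96) = 94.0% (93.8% by the t-test). The plan says "we have 93% power to detect a 5-point difference in change from baseline in the DASH score at Day 90".
- Between education arms: SE = 9 × √(1/100 + 1/100) = 1.273; 5/1.273 = 3.928; power = Φ(1.968) = 97.5% (97.4% by t). The plan states 97%.
- Table 5 by t-test: 80.1, 76.9, 68.9, 66.1 and 56.2%, against 80, 77, 69, 66 and 56%.

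The plan's figures reproduce, so SD 9 and two-sided 0.05 are carried forward.

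**2. Subgroup shares.** The documents do not give them. With a common residual SD, n is proportional to 1/(CI half-width)², so Table S20 implies them approximately.

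| Smaller group | Half-widths, education arms | Share (of 201) | Half-widths, control | Share (of 46) | Pooled share p |
|---|---|---|---|---|---|
| Age 21-50 | 3.25 v 1.60 | 19.5% (39) | 5.20 v 3.55 | 31.8% (15) | 0.218 |
| DASH <40 | 2.55 v 1.65 | 29.5% (59) | 5.45 v 3.45 | 28.6% (13) | 0.293 |
| Not obese | 2.25 v 1.95 | 42.9% (86) | 5.40 v 3.70 | 31.9% (15) | 0.409 |

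The same widths imply a residual SD a little above the plan's. For age 21-50, 3.25/1.96 × √39.2 = 10.4. SD 9 and SD 11 are therefore both shown; SD 11 is an assumption.

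**3. Formula.** Assume a normally distributed factor and an effect linear in it. Let z be the cut at share p, φ the normal density, and D the difference in treatment effect between the two cut groups.

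- Cut test: ncp = D × √[p(1 − p)] / [SD × √(1/46 + 1/201)].
- Share of information kept by the cut: r = φ(z)²/[p(1 − p)], which is 0.509 (age), 0.571 (DASH) and 0.624 (BMI).
- Continuous test: ncp = cut ncp/√r.
- Power = Φ(ncp − 1.96) + Φ(−ncp − 1.96).

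The denominator is 9 × 0.16345 = 1.471, or 11 × 0.16345 = 1.798.

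Example, age with D = 8 and SD 9: cut ncp = 8 × √(0.218 × 0.782)/1.471 = 2.245, power 61.2%. Continuous ncp = 2.245/√0.509 = 3.148, power 88.3%.

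| Factor | D | SD 9: continuous v cut (loss) | SD 11: continuous v cut (loss) |
|---|---|---|---|
| Age | 3 | 21.9 v 13.4% (8.5) | 16.2 v 10.6% (5.6) |
| Age | 5 | 50.3 v 28.9% (21.4) | 36.3 v 20.9% (15.4) |
| Age | 8 | 88.3 v 61.2% (27.1) | 73.1 v 45.1% (28.0) |
| DASH | 3 | 23.3 v 15.3% (8.0) | 17.1 v 11.8% (5.3) |
| DASH | 5 | 53.5 v 34.0% (19.5) | 38.8 v 24.4% (14.4) |
| DASH | 8 | 90.6 v 69.7% (20.9) | 76.4 v 52.6% (23.8) |
| BMI | 3 | 24.5 v 17.1% (7.4) | 18.0 v 13.0% (5.0) |
| BMI | 5 | 56.2 v 38.6% (17.6) | 40.9 v 27.7% (13.2) |
| BMI | 8 | 92.3 v 76.2% (16.1) | 79.1 v 59.0% (20.1) |

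**4. Simulation** of the linear case (201 v 46, SD 9), continuous v cut:

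- D = 8: age 85 v 55%, DASH 89 v 64%, BMI 90 v 71%.
- D = 5: age 49 v 28%, DASH 51 v 32%, BMI 57 v 39%.

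The losses are 18 to 30 points.

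**5. Reverse case.** If the effect is an 8-point step exactly at the cut (200 v 50, SD 9), simulated power for cut v continuous is age 62 v 36%, DASH 72 v 46%, obesity 78 v 56%.

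**6. What the two non-significant interactions rule out.** Treating the Table S20 subgroups as independent:

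- DASH: 4.3 − 3.3 = 1.0, ± √(6.1² + 3.9²) = 7.2, so about −6 to 8.
- Obesity: 4.1 − 0.9 = 3.2, ± √(5.85² + 4.5²) = 7.4, so about −4 to 11.

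Neither excludes 5 points, the difference on which the trial was sized.

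**The case against.** **No decision depends on it.** The subgroup analyses are exploratory, the note to protocol Table 5 says that alpha is not held at 0.05 for secondary analyses, and the primary and second-step tests do not use these cuts. This stands, and it makes the point a cheap improvement rather than a flaw in the trial's main conclusion.

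**The SAP specified no interaction test.** A reader might infer that the SAP prescribed weak tests. It did not: the tests appear only in Table S20 and its footnote. The SAP's part is that it plans two-level rows only and leaves the model unstated.

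**The cuts are not all arbitrary.** BMI 30 is the trial's own inclusion threshold and the SAP's definition of obesity. The two age groups also appear in the SAP baseline table, and age-group is a covariate in its models. Only DASH 40 has no visible basis. This stands, but a familiar threshold does not restore the lost information.

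**The shares are approximate.** They come from CI widths in an analysis that used imputed values. Giving each arm its own age share (19.5% and 32%) in simulation at SD 9 lowers the age loss to 20 points at D = 8 and 16 at D = 5. Doing the same for BMI raises its loss at D = 8 from 16 to 24. These stay within the range given.

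**The continuous test is not always better.** It rests on linearity, and step 5 shows the ranking reversing under a step. This stands, so the continuous p-value should not be the only one reported.

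**The fix might not change Table S20.** A reader might infer that baseline DASH or obesity would have reached significance. The documents do not support that. At the observed differences of 1.0 and 3.2 points, continuous v cut power is about 7 v 6% and 26-27 v 17-18%. For age, the cut did detect an interaction (p<0.01).

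**Conclusion.** The point holds as a modest one. The SAP subgroup table looks at effect modification by age, BMI and baseline DASH only through two-level cuts, and the reported interaction tests used them. For subgroup differences of 5 to 8 DASH points, the cut test has about 15 to 30 points less power than a continuous one (13 to 28 by formula, 18 to 30 by simulation). For differences of about 3 points or fewer the loss is under 10 points.

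This rests on a linear gradient, a normally distributed factor, SD 9 to 11, and shares inferred from Table S20. The documents state no interaction effect size, so D is assumed throughout. Under a step at the cut, the cut test is the stronger one.

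A reader might put the loss as high as 35 points. At the implied shares the formula's maximum over all effect sizes is 28.5 (age), 23.8 (DASH) and 20.2 (obesity); a maximum near 35 needs a split of about 15/85. Nothing here bears on the primary test.

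**What to change.** In the SAP subgroup section, for age, BMI and baseline DASH:

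- Prespecify the interaction of the continuous baseline value with treatment (POP1/POP2 v Control) as the main test of effect modification, and name the model. An analysis of covariance of the 3-month score, with the baseline value and its product with treatment, would serve.
- Report the interaction slope with its 95% CI, and the fitted treatment effect at two or three stated values of the factor.
- Keep the two-level rows, with their interaction result, as a supporting display and a check on linearity. Report both results whichever way they fall.
- Say that these analyses remain exploratory.

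The cost is SAP wording and three extra model terms; no new data are needed. The downside is that the continuous test assumes a roughly linear gradient, which is why the two-level result stays beside it.
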